### *Immunology*

Preliminary studies have shown a baseline level of IFN-g at 69 pg / ml. With 200 vaccinated and 200 controls we will be able to detect a 25% increase in IFN-g, and a 25% increase in IL-10 from 18 to 24 pg / ml.

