## METHODS

### Study site

The Bandim Health Project (BHP) has a demographic surveillance system in several districts of the capital of Guinea-Bissau, and the current population in these districts is around 80.000. All houses in the area are visited every month to register new pregnancies and births. The BHP visits all children at home every 3 months until the age of three years. Information is collected routinely on breastfeeding patterns, infections, hospitalisation, vaccination status, living with the mother, and ownership of pigs. The people of Bissau are travelling a lot due to extended families living in other parts of the country, cashew harvest, and trade. About 20% of the mothers are travelling at any given time. About 2.600 children are born in the BHP study area each year, and experience shows that we will be able to enrol about 80% of these in a measles vaccine trial i.e. about 2.000 infants per year.

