### *Time table*

The study is planned to begin in January 2005 with a recruitment period of about 8 months. Since season has a large influence on health in West Africa on both morbidity and mortality, as well as immunologic parameters such as delayed-type hypersensitivity, T-cells, thymus size and measles antibody levels, it will be desirable to spread out the sample collection to cover both seasons of the year. Thus, we plan to include 25 children to be measles vaccinated per month, and 25 controls alternating from arm II and arm III.

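### The immunology sample size describes IL-10 rising from 18 to 24 pg/ml as a 25% increase; it is 33%, and 25% above 18 is 22.5 pg/ml

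*Protocol*

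**What the plan says.** The immunology part of the protocol's Sample size section is two sentences long. The first gives a starting level for one cytokine: "Preliminary studies have shown a baseline level of IFN-g at 69 pg / ml". The second makes two detectability claims for the same group sizes. For IFN-γ it reads "With 200 vaccinated and 200 controls we will be able to detect a 25% increase in IFN-g", and for IL-10 it adds "a 25% increase in IL-10 from 18 to 24 pg / ml". Neither sentence gives a standard deviation, measurement scale, significance level or power. The 80% power figures in that section belong to the morbidity and hospitalisation calculations.

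On numbers and timing, the Time table section says "The study is planned to begin in January 2005 with a recruitment period of about 8 months" and "we plan to include 25 children to be measles vaccinated per month, and 25 controls alternating from arm II and arm III". The Analysis section puts the emphasis on change between the first and second blood sample in the two groups. The section on additional procedures for the immunological study places the second sample six weeks after the first, at the child's home. The Study site section says of the surveillance population: "About 20% of the mothers are travelling at any given time".

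**The concern.** A detectable effect given both as a percentage and as two levels should agree with itself. Here it does not, and the two readings are different targets: a difference of 4.5 pg/ml for a 25% increase, or 6 pg/ml for 18 to 24. Without an SD or a power, nothing else in the paragraph shows which of them 200 per group was meant to deliver. IL-10 and IFN-γ are the only immunological effects that the protocol quantifies, so half of the stated immunological justification cannot be read as written.

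A smaller matter sits beside it. The number assumed in the calculation appears to equal the number enrolled, although the analysis of change can only use children who also give the later sample.

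**Working it through.** **Inputs.** IL-10 levels 18 and 24 pg/ml, stated increase 25%, 200 per group (Sample size, Immunology). Recruitment of 25 per group per month for about 8 months (Time table). Assumed here because the paragraph gives neither: two-sided alpha 5% and 80% power, so z = 1.96 + 0.84 = 2.80.

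**1. The stated percentage.**
- 18 to 24: (24 − 18)/18 = 33.3%. The stated 25% is not reproduced.
- 25% above 18: 18 × 1.25 = 22.5 pg/ml.
- Rounding: if both levels were rounded to whole numbers, the smallest compatible increase is 18.5 to 23.5, and 23.5/18.5 = 1.27, or 27%.
- Other denominator: (24 − 18)/24 = 25%, but that describes a fall from 24 to 18.

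No variant gives a 25% increase.

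**2. What each reading implies.** With n per group, the SD at which the effect has 80% power is effect / (2.80 × √(2/n)). At n = 200 the divisor is 2.80 × 0.1 = 0.280.
- Calculated for 18 to 24: SD = 6/0.280 = 21.4 pg/ml, or ln(24/18)/0.280 = 1.03 on the log scale.
- Calculated for 25%: SD = 4.5/0.280 = 16.1 pg/ml, or ln(1.25)/0.280 = 0.80 on the log scale.

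**3. Consequence under each reading.**
- If 200 per group was derived for 18 to 24, power for a true 25% increase is Φ(2.80 × 4.5/6 − 1.96) = 56% on the raw scale, or Φ(2.80 × 0.223/0.288 − 1.96) = 58% on the log scale. Restoring 80% would need 356 or 333 per group.
- If 200 per group was derived for 25%, the design has the assumed 80% for that effect. Then 24 is a slip for 22.5, and no power is lost.

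**4. Enrolment and second samples.** 25 × 8 = 200 per group, equal to the number in the calculation. The protocol states no loss rate, so the loss below is an assumed range. Power is Φ(2.80 × √(n/200) − 1.96), and the detectable increase is 25% × √(200/n).

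| Assumed loss | Second samples per group | Power, from 80% | Detectable increase, from 25% |
|---|---|---|---|
| 5% | 190 | 78% | 25.6% |
| 10% | 180 | 76% | 26.4% |
| 20% | 160 | 71% | 28.0% |

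Keeping 200 second samples per group would need 200/(1 − loss), rounded up: 211, 223 or 250 enrolled per group.

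**The case against.** The arithmetic error has no defence. The case on the other side concerns what may be built on it, and most of that case stands.

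- **Power.** A reader might infer that the study would miss a true 25% rise in IL-10 more than four times in ten. That follows only if the calculation used 18 to 24, and only under the assumed 80% power and 5% test. The documents do not show that it did. The opposite reading, a misprinted 24, is equally compatible with the text and costs nothing.
- **Loss to the second sample.** A reader might take the travelling figure as a 20% loss, leaving 160 pairs per group. The protocol does not say this. The figure is the share of mothers away at any one time, not a rate of missed samples. Enrolled children have already attended the health centre. The Morbidity survey section has these same children visited five times in the first two weeks and then weekly until 9 months of age, which gives repeated chances to find a child. So 20% is probably an upper value. The sample size paragraph also never says that its 200 are pairs; that need comes from the Analysis section. What remains is that enrolment and the calculation use the same number, with no visible reserve.
- **Sex.** A reader might ask for detectable effects within boys and girls. The protocol makes no power claim by sex, so nothing there is misstated.
- **Weight.** The Analysis section calls the work essentially explorative. The same 200 per group also serves the IFN-γ target and the morbidity calculation, and no decision rule depends on the IL-10 figure. This lowers the severity but does not make the sentence correct.

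**Conclusion.** The IL-10 statement contradicts itself: 18 to 24 pg/ml is a 33% increase, and a 25% increase from 18 reaches 22.5 pg/ml. This is certain and rests on no assumption. Its effect on power is open. It ranges from none, if 25% was calculated, to 56–58% power for a true 25% increase, if 18 to 24 was calculated with 80% power at a two-sided 5% level. Only the sponsor can say which applies.

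The point about second samples is secondary and softer. Planned enrolment is approximate, because the recruitment period is given as about 8 months, and the 5–20% loss is an assumption. Within that range the effect is modest: 25% becomes about 26–28%, or 80% power becomes about 78–71%. Overall severity is minor to moderate.

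**What to change.** In the immunology part of the Sample size section, replace the IL-10 statement with whichever was calculated: 33% (18 to 24 pg/ml), or 25% (18 to 22.5 pg/ml). Give the SD, the scale (raw or log), alpha and power behind it, so that a reader can reproduce 200 per group.

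In the same paragraph, state how many second samples per group the sponsor expects, using its own experience of the six-week home visit, and restate the detectable effect for that number. The loss rate should be the sponsor's, not one borrowed from the travelling figure.

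The cost is a change of protocol wording. Neither the design nor the planned enrolment has to change, though the stated detectable effect may become slightly less favourable.

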### *Time table*

The study is planned to begin in January 2005 with a recruitment period of about 8 months. Since season has a large influence on health in West Africa on both morbidity and mortality, as well as immunologic parameters such as delayed-type hypersensitivity, T-cells, thymus size and measles antibody levels, it will be desirable to spread out the sample collection to cover both seasons of the year. Thus, we plan to include 25 children to be measles vaccinated per month, and 25 controls alternating from arm II and arm III.

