| All                                                                                                           | 0 (0/677)                                  | 0.01 (16/1345)                             | 0 (0-0.52)                              |
| Hospitalisation for non-
measles infections                                                               |                                            |                                            |                                         |
| Male                                                                                                          | 0.02 (8/333)                               | 0.03 (20/698)                              | 0.84 (0.32-1.99)                        |
| Female                                                                                                        | 0.01 (5/344)                               | 0.04 (29/647)                              | 0.32 (0.10-0.85)                        |
| All                                                                                                           | 0.02 (13/677)                              | 0.04 (49/1345)                             | 0.53 (0.26-0.99)                        |

The proposed study will be conducted as an immunological study performed among a subgroup of the participants in the above study.

Procedures, measles vaccination trial

Newborn infants are identified in the BHP registration system. To make sure that all children have received three doses of DTP before inclusion in the Two-dose trial, we contact the mothers of 6, 10 and 14 weeks old children, and remind them to go to the local health centre to receive the DTP

vaccine. The formal inclusion in the Two-dose trial is at 4½ months of age. During the morning hours field-workers contact the mothers/guardians of the children to be included in the study. The field-workers explain about the study, perform a questionnaire, and obtain verbal consent (please refer to ethical considerations).

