#### *Sample size*

##### *Morbidity*

With an expected diarrhea frequency of 6 episodes per year for children under 3 years (36), we can assume that each child will have at least one episode of diarrhea or fever between 4 ½ and 9 months of age. With 200 vaccinated and 200 unvaccinated children followed for morbidity, we will with a power of 80% be able to find a 20% reduction in infection incidence.

Preliminary results indicate a 50% reduction in hospitalization rates for measles vaccination at 4 ½ months (table). Not only those who have taken the blood test, but all children (n = 5,755) included in the study will be registered in terms of hospitalizations. One third of the children enrolled at 4 ½

months will receive measles vaccine immediately, and 2/3 will receive measles vaccine at 9 months of age. With 765 vaccinated at 4 ½ months and 1,530 unvaccinated (who will receive the vaccine at 9 months) we will be able to find a 50% reduction in hospitalization with 80% power.

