## **ETHICAL CONSIDERATIONS**

The two-dose study of measles vaccination was approved by the Ministry of Health in Guinea-Bissau, the MRC Ethical Committee and the Scientific Coordinating Committee at the MRC in The Gambia, and by the Danish Central Ethical Committee. The present protocol will be submitted to the same committees.

Mothers/guardians will be informed about the measles vaccination trial shortly before the child reaches 4½ months of age (see Procedures, measles vaccination trial). Since most mothers are illiterate there is no tradition for written consent in the study area. However, mothers who feel

confident will be asked to sign, and those who cannot write will be asked to confirm their participation by fingerprint. Mothers accepting to participate will be asked to draw a lot to emphasise that the study is a randomised trial. The mothers will be asked to consent to participate after having received an explanation, which will contain the following information verbally (Portuguese Creole) and in print (Portuguese):

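### The sub-study is filled by monthly quotas per allocated arm, with no stated rule for which children are taken within an arm and no placing of sub-study consent before the lot

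*Protocol*

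**What the plan says.** The immunological study is to be "performed among a subgroup of the participants in the above study", that is, of the running measles vaccination trial. The Time table gives the intake as "we plan to include 25 children to be measles vaccinated per month, and 25 controls alternating from arm II and arm III", over a "recruitment period of about 8 months". Sample size (Immunology) plans on the resulting groups: "With 200 vaccinated and 200 controls we will be able to detect a 25% increase in IFN-g". Sample size (Morbidity) uses the same 200 and 200 to seek a 20% reduction in infection incidence with 80% power.

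The parent trial has a different ratio. Sample size (Morbidity) starts from "One third of the children enrolled at 4 ½" months being vaccinated at once, while "2/3 will receive measles vaccine at 9 months of age". The Objectives set measles vaccine against no vaccine at 4½ months, and no placebo is described. Under Ethical considerations, "Mothers accepting to participate will be asked to draw a lot to emphasise that the study is a randomised trial".

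Additional procedures puts the first blood sample at the health-centre visit at which arm I is vaccinated. Analysis then compares the two groups' changes from first to second sample to assess the effect of the vaccine, and relates them to morbidity up to 9 months.

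**The concern.** Randomisation protects the comparison of all children in arm I with all children in arms II and III. It protects a comparison of subsets only if entry to the subset is unrelated to prognosis in the same way in both groups. That can be secured by deciding entry before the arm is known, or by a rule within each arm that neither staff nor mothers can influence. The protocol states neither.

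Without a placebo, mother and staff can know the arm once the lot is drawn. If the quotas are filled after that, staff may take children who are well or easy to find, and mothers may accept or refuse two finger-pricks and close follow-up, differently according to whether the child was vaccinated. Study site notes that about 20% of mothers are travelling at any time, so ease of finding a child is a practical matter. Health and availability bear directly on recorded illness, so a selection difference could be read as a vaccine effect.

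**Working it through.** **Inputs.** Quotas of 25 and 25 per month and about 8 months (Time table); 200 and 200 (Sample size); allocation of 1/3 and 2/3 (Sample size, Morbidity); accrual "in a measles vaccine trial i.e. about 2.000 infants per year" (Study site).

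**1. The plan's own figure.** 25 × 8 = 200 per group. The quotas yield the planned size, so the 1:1 ratio is intended.

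**2. The parent ratio.** The preliminary hospitalisation table has 677 vaccinated and 1,345 unvaccinated children: 677/(677 + 1,345) = 33.5%, in agreement with 1:2.

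**3. Fraction taken.** Monthly accrual is 2,000/12 = 166.7, of which 166.7/3 = 55.6 in arm I and 111.1 in arms II and III together.
- Arm I: 25/55.6 = 45% taken, 55% not taken.
- Controls: 25/111.1 = 22.5% taken, 77.5% not taken.
- Children passed over per child taken: (55.6 − 25)/25 = 1.2 in arm I and (111.1 − 25)/25 = 3.4 in controls.

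**4. Sensitivity to accrual.** Using 80% of 2,600 births (2,080 per year), the fractions are 43% and 22%. The trial has recruited 2,025 children since August 2003. The date of that count is not given; assuming 12 to 17 months gives 169 to 119 children per month, hence 44% to 63% of arm I and 22% to 31% of controls. The ratio of the two fractions is always 2.

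**5. What the fractions imply.** A 25:25 sample cannot be obtained from a 1:2 trial without using the arm. That does not show how the arm is used. If children are taken at random or consecutively within each arm, or through lots marked in advance, the comparison stays valid at any pair of fractions. The gap is the missing rule.

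**6. How much it could matter (assumed values, not estimates).** Let a share q of the chosen vaccinated children and 2q of the chosen controls have a trait that multiplies the episode rate by r. With no true effect the expected rate ratio is (1 − q + qr)/(1 − 2q + 2qr).

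| q | r = 1.25 | r = 1.5 | r = 2 |
|---|---|---|---|
| 0.10 | 0.976 | 0.955 | 0.917 |
| 0.20 | 0.955 | 0.917 | 0.857 |

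For q = 0.10 and r = 1.5: (0.9 + 0.15)/(0.8 + 0.30) = 1.05/1.10 = 0.955. The spurious reduction runs from about 2% to 14%, against the 20% sought. If the imbalance ran the other way, the ratios would be the reciprocals, about 1.02 to 1.17. The documents give no basis for the doubling, for r or for the direction.

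**7. Ignoring the arm altogether.** Taking 400 children regardless of arm would give about 133 and 267. Effective information is 1/(1/133 + 1/267) = 88.8, against 1/(1/200 + 1/200) = 100 for 200 and 200, a loss of about 11%. Matching it would need 150 and 300. There is therefore a good reason to keep 1:1, provided the selection is protected.

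**The case against.** The sentence in the Time table is an accrual plan meant to spread sampling over the seasons. It does not say that staff choose freely or that children are picked after the lot. Arm-dependent sampling can be arranged in advance, so one cannot conclude that selection must follow disclosure. The consent information is not in the copy available, and it may place agreement to blood sampling before the lot. All of this stands: selection after the lot, and mothers knowing the arm when they agree to the sub-study, are inferences. What remains is that the text available does not exclude either.

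A reader might infer three stronger things, none of them supported:
- **That alternation is a flawed allocation.** It runs between arms II and III, both without measles vaccine until 9 months and together forming one control group. It does not decide who is vaccinated.
- **That the unequal fractions, or the children not taken, are bias.** Those children stay in the parent trial, and unequal sampling within randomised arms is harmless if unrelated to prognosis.
- **That the sub-study groups are biased or no longer randomised.** The documents show only that they are not protected.

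There are also safeguards. Children ill enough to need admission join only after recovery, whatever their arm. The cytokine analysis uses change from a first sample taken at the inclusion visit, and the protocol calls it exploratory. Hospitalisation is recorded for all trial children. These narrow the exposure but do not cover the sub-study morbidity comparison, for which no baseline is described.

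**Conclusion.** The point holds as a gap in the design. Arm-specific 1:1 quotas are drawn from a 1:2 trial without placebo, taking about 45% of arm I and 22% of controls (up to about 63% and 31% if accrual is slower). No stated rule governs the choice within arms, and sub-study consent is not placed in relation to the lot. The sub-study morbidity comparison is the main one exposed, the cytokine changes are partly exposed, and hospitalisation is not.

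The size of any bias is unknown; the assumed examples show only that a moderate imbalance could mimic part of a 20% effect. The conclusion rests on the text available, from which the consent information is missing. It is a matter of design rather than analysis: adjustment for measured baseline factors cannot fully undo an uncontrolled selection. It is worth correcting because the remedy is cheap.

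**What to change.** Amend Additional procedures, Time table and Ethical considerations as follows.

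1. Fix entry to the sub-study before allocation. Someone not involved in recruitment marks the outside of closed lots, with the arm hidden inside: a random share of arm I lots and half that share of arm II and arm III lots. At 2,000 per year, 45% and 22.5% would do. Marked lots are then 0.45 × 1/3 + 0.225 × 2/3 = 30% of all lots, split 1:1, or 166.7 × 0.30 = 50 per month. The parent trial stays at 1:2. The shares should be raised for slower accrual or expected refusal.
2. For a child with a marked lot, obtain consent to the extra blood samples and morbidity visits, and take the first sample, before the lot is opened. This fits the existing visit, since the first sample and arm I vaccination already share it.
3. Include every consenting child with a marked lot, and record refusals.
4. Compare baseline characteristics, including health at inclusion, by group.

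The cost is the preparation of the lots, a fixed order of steps at the visit, and monthly counts that vary slightly around 25 and 25. No extra children are needed beyond any allowance for refusal, and about 200 per group is kept.

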### *Analysis*

The analysis will emphasise changes in immunological parameters between the first and second sample for the two groups to assess the effect of a measles vaccine after DTP controlling for age related changes. Possible differences between boys and girls will be examined. This analysis is essentially an explorative investigation to detect immunological changes which might explain the differential effects of DTP and measles vaccine. At the same time, it will be investigated whether these potential differences in cytokine profile correlate with differences in morbidity between 4½ and 9 months of age when all children receive measles vaccine.

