#### *Additional procedures, proposed immunological study*

In the proposed study it is planned to perform the first blood sample on the first contact at the health centre at 4½ months of age. At this age, all the children have received the third dose of DTP. On the same occasion, participants in arm I will receive a measles vaccine. Six weeks after this occasion (at 6 months of age), a blood sample will be obtained at home. Children enrolled in the immunological study will be included in a morbidity study to be able to assess the possible correlation between differences in cytokine profile and morbidity.

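### The immunological analysis compares changes between samples without adjusting for the first-sample value, which is unbiased but gives away precision at no benefit

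*Protocol*

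**What the plan says.** The protocol's Analysis section fixes the compared quantity: "The analysis will emphasise changes in immunological parameters between the first and second sample for the two groups". The stated purpose is to assess measles vaccine given after DTP while allowing for changes that come with age. The section names no regression model, covariate or measurement scale, and does not mention the first-sample value as a covariate. It also states the status of the work: "This analysis is essentially an explorative investigation to detect immunological changes".

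The section on additional procedures for the immunological study sets the two time points. For the first, "it is planned to perform the first blood sample on the first contact at the health centre at 4½ months of age", which is also when arm I is vaccinated. For the second, "Six weeks after this occasion (at 6 months of age), a blood sample will be obtained at home".

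The comparison is randomised. Under Ethical Considerations, "Mothers accepting to participate will be asked to draw a lot to emphasise that the study is a randomised trial". The subgroup is sampled one to one: "Thus, we plan to include 25 children to be measles vaccinated per month, and 25 controls alternating from arm II and arm III".

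The Immunology part of the sample-size section says "Preliminary studies have shown a baseline level of IFN-g at 69 pg / ml" and "With 200 vaccinated and 200 controls we will be able to detect a 25% increase in IFN-g". It gives no SD, significance level, power or within-child correlation. It does not say whether the calculation concerns a level or a change.

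**The concern.** A change score subtracts the whole first-sample value, which implies that a child who starts one unit higher is expected to end one unit higher. When the within-child correlation is below 1 and the SDs are equal, the expected carry-over is smaller than that, so the subtraction adds noise. Regression on the first-sample value estimates the carry-over from the data instead of fixing it at one.

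The stated purpose does not require subtraction. The controls are sampled at the same two ages, so the comparison between groups already removes age-related change.

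What is at stake is precision in the study's main immunological comparison. The same loss carries into the planned look at boys and girls, where each estimate rests on fewer children.

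**Working it through.** **The plan's own figure.** The planned IFN-γ effect is 25% of 69 pg/ml, that is 0.25 × 69 = 17.25 pg/ml, with 200 per group. It cannot be reproduced because the SD, significance level and power are missing. Assuming two-sided 5% and 80% power, the implied SD is 17.25 / [(1.96 + 0.84) × √(2/200)] = 61.6 pg/ml, a coefficient of variation of 61.6/69 = 0.89. Nothing shows whether this SD would belong to a level or to a change.

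**Same target.** The first sample is taken at the vaccination contact, so the vaccine cannot have affected it. Under randomisation its expected value is the same in both groups, and both methods estimate the same vaccine effect.

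**Variances.** Let s1 and s2 be the SDs at the first and second samples. Per child:

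- change: s1² + s2² − 2·r·s1·s2
- second sample adjusted for the first: s2²(1 − r²)
- second sample alone: s2²

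Change minus adjusted equals (s1 − r·s2)². This is never negative, and is zero only when r = s1/s2. With equal SDs set to 1, the variances are 2(1−r), 1−r² and 1, and the ratio of change to adjusted is 2(1−r)/[(1−r)(1+r)] = 2/(1+r). Estimating one slope from about 400 children costs a negligible amount.

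**Size over an assumed range of r.** If the adjusted analysis has 80% power at two-sided 5%, the power of the change comparison is Φ(2.80 × √[(1+r)/2] − 1.96):

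| r (assumed) | Change, 2(1−r) | Adjusted, 1−r² | Ratio | Power of change if adjusted has 80% |
|---|---|---|---|---|
| 0.2 | 1.60 | 0.96 | 1.67 | 58% |
| 0.3 | 1.40 | 0.91 | 1.54 | 62% |
| 0.5 | 1.00 | 0.75 | 1.33 | 68% |
| 0.7 | 0.60 | 0.51 | 1.18 | 73% |

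**Other reference points.** The power figures depend on which method is taken to have 80%, so two alternatives are shown, each with 200 per group.

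| r (assumed) | Second sample alone at 80%: change | Second sample alone at 80%: adjusted | Change at 80%: adjusted |
|---|---|---|---|
| 0.2 | 60% | 82% | 95% |
| 0.3 | 66% | 84% | 94% |
| 0.5 | 80% | 90% | 90% |
| 0.7 | 95% | 97.5% | 86% |

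A simulation of the first alternative (4,000 runs, 200 per group) gave 60%, 65%, 80% and 96% for change, and 80%, 83%, 90% and 98% for adjusted. The adjusted analysis has the higher power in every row, and only the size of the gap depends on the reference.

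**Change against the second sample alone.** With equal SDs the change is the noisier when 2(1−r) > 1, that is r < 0.5. With k = s2/s1 the threshold is r < 1/(2k): about 0.63 at k = 0.8 and 0.33 at k = 1.5.

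**The case against.** The strongest reply is that the protocol names no model. Regressing the change on group and first-sample value fits an emphasis on changes, and it gives the same group coefficient as regressing the second-sample value on both: subtracting the baseline from each side of the equation alters only the baseline slope. Model detail may also be left to a statistical analysis plan. The algebra stands, and it shows how small the repair is. It does not remove the point, because the protocol does choose the compared quantity and mentions no baseline adjustment. Followed as written, it gives the less precise comparison.

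The exploratory label also stands, and it lowers the weight of the point.

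A reader might infer four stronger things, none of which the protocol supports:

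- *That change scores are biased.* Under randomisation they are not. Carrying a chance baseline difference into the result is the same loss of precision seen from another side.
- *That the plan does worse than ignoring baseline.* This needs r below about 0.5, and the protocol gives neither r nor the SDs. At r = 0.7 the change clearly beats the second sample alone (95% against 80%).
- *That the detectable differences in the sample-size section are shown to be out of reach.* They have no stated SD, significance level, power or basis. If they were calculated for changes, there is no shortfall against the plan.
- *That raw pg/ml changes clash with effects given in percent.* The Analysis section states no scale.

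**Conclusion.** The point holds as one of efficiency, not validity. The emphasised comparison has 1.18 to 1.67 times the variance of the baseline-adjusted one for r between 0.7 and 0.2. Put the other way, it uses (1+r)/2 of the available information, from 85% down to 60%.

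The direction holds for any r below 1 with equal SDs; with unequal SDs the two methods tie only when r = s1/s2. The size rests on three assumptions: the range of r, equal SDs at the two samples, and selection into the subgroup that keeps the groups comparable at baseline. The power figures also assume two-sided 5% and a chosen reference method.

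This is a free improvement of modest priority in an analysis that calls itself exploratory.

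**What to change.** Add to the Analysis section wording such as:

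> The second-sample value (or, equivalently, the change from the first sample) will be compared between the groups by linear regression with the first-sample value as covariate, both on the same scale, log-transformed if skewed. Unadjusted changes will be presented descriptively.

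The implied coefficient of variation near 0.9 suggests that skewness is likely, but the scale should be settled on the data or on pilot results. Further adjustment for sex or month of inclusion, and a group-by-sex term, are optional and do not follow from this point.

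The cost is one sentence. Both samples are already planned, so no extra visit, blood volume or assay is needed.
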